### Recruitment

2.4

All patients consisted of outpatients and inpatients with essential hypertension in the Department of Cardiovascular Medicine of Chengdu Fifth People's Hospital from July 2017 to July 2018. Consent will be obtained by the investigators with the principle of informed consent, which confirms the participants’ voluntarism. The participants will sign the consent form that would include the information on the use of their blood sample, urine sample, ambulatory blood pressure data, and echocardiography results.

### Outcome measures

2.5

According to the schedule depicted on Table 1, we will use a series of outcome measures.

**Table 1 T1:**
[figure not shown]
Study schedule for data collection and outcome measures.

#### Questionnaire

2.5.1

The participants will complete a questionnaire that would include general sociodemographic information (e.g., age and sex), personal habits (e.g., smoking, alcohol consumption, sleep pattern, and dietary habits), anthropometric measurements (e.g., height, weight, and BMI), pregnancy, menstrual pattern and history, history of present illness, medication history, history of hypertension in relatives, and relevant comorbidities (e.g., cerebrovascular disorders, heart failure, coronary disease, chronic renal failure, and aortic disease).

#### Blood pressure determination

2.5.2

The patient begins to measure blood pressure after resting for 5 minutes in a quiet room. No matter what position the patient is in, the upper arm should be placed at the heart level. The systolic blood pressure (SBP) and diastolic blood pressure (DBP) were determined using the Corson sounds 1st and 5th, respectively, and each person's blood pressure was measured at least 2 times at intervals of 1 to 2 minutes. If there is a big difference between the 2 measurements, we will measure again.

#### Ambulatory blood pressure monitoring

2.5.3

All subjects used a fully automatic noninvasive cuff blood pressure monitor (fixed model) for blood pressure monitoring. The cuff is fixed to the subject's left upper arm and can be used for daily work and activities, but strenuous exercise should be avoided. Monitoring time: measured every 30 minutes during the day (8:00–22:00), every night at 22:01 to 7:59 the following day, every hour. The daily effective blood pressure reading is greater than 85% of the set number, and the effective value needs to be greater than 48 times. Effective blood pressure readings: SBP 70–260 mm Hg (1 mm Hg = 0.133 kPa), DBP 40 ∼ 150 mm Hg, pulse pressure 20 ∼ 120 mm Hg. Monitoring indicators: 24-hour mean SBP (24-h SBP), 24-hour mean DBP (24-h DBP), day-time mean SBP, night-time mean SBP, day-time average DBP, and night-time mean DBP. The blood pressure standard deviation (SD) and its coefficient of variation (CV) at each time period were used as indicators of BPV at that time period. (CV-SBP, coefficient of variation of systolic blood pressure) CV is the ratio of the SD to the mean. Expressed by the formula: CV = σ/μ. Monitoring normal reference value: 24 hour mean blood pressure <130/80 mm Hg, daytime blood pressure <135/85 mm Hg, nocturnal blood pressure <120/70 mm Hg. Blood pressure circadian rhythm = (average blood pressure during the day − average blood pressure during the night) / average blood pressure during the day; >10% is normal blood pressure circadian rhythm (dipper type hypertension), otherwise it is nondipper type hypertension, <0 is the anti-dipper type hypertension; CV-SBP is grouped with a cutoff of 12%.

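### ABPM completeness is tested only over the whole day, so the one condition the schedule can meet, the 85% clause, does not protect the night indices

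*Protocol article*

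**What the plan says.** Everything relevant is in section 2.5.3 (Ambulatory blood pressure monitoring) of the protocol article.

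- Schedule: "measured every 30 minutes during the day (8:00–22:00), every night at 22:01 to 7:59 the following day, every hour".
- Completeness, first condition: "The daily effective blood pressure reading is greater than 85% of the set number".
- Completeness, second condition, in the same sentence: "and the effective value needs to be greater than 48 times".
- Range checks on single readings, beginning "Effective blood pressure readings: SBP 70–260 mm Hg", with similar limits for diastolic and pulse pressure.
- Use of the data: "The blood pressure standard deviation (SD) and its coefficient of variation (CV) at each time period were used as indicators of BPV", separately by period. Dipping status is the day mean minus the night mean, divided by the day mean, with cutoffs at 10% and 0.

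The section gives no separate minimum for day or for night.

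**The concern.** The validity rule works on the whole recording, while the indices it feeds are computed by period. About three quarters of the scheduled readings are daytime, so a full daytime record can carry a poor night past a pooled percentage. The night mean, night SD, night CV and dipping class would then rest on few readings, although the rule suggests at least 85% completeness.

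Blood pressure variability is one of the three quantities the study sets out to relate. An SD from four or five readings is a noisy measure, and noise in a variability index tends to weaken its correlation with sodium excretion and target organ damage.

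The rule also has a fault that comes first: its absolute count does not fit the schedule, so the sentence has to be edited in any case.

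**Working it through.** **Scheduled readings.** Half-hourly from 8:00 to 22:00 is 14 × 2 = 28 readings, or 29 if both endpoints count. Hourly from 22:01 to 7:59 is 9 readings (23:00 to 7:00) or 10 (22:01, 23:01, … 7:01). The total is 37 to 39.

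**The absolute count.** More than 48 means at least 49. The schedule gives at most 39, so even a complete recording falls short by at least 49 − 39 = 10. For 85% of the schedule to equal 48, about 48 / 0.85 = 56 readings would have to be scheduled. The stated count therefore cannot be reproduced from the stated schedule under any way of counting the endpoints.

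**The 85% clause.** The minimum valid number is floor(0.85 × total) + 1. The fewest night readings are that minimum less a complete daytime.

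| Day | Night | Total | 85% | Minimum valid | May be lost | Fewest night readings |
|---|---|---|---|---|---|---|
| 28 | 9 | 37 | 31.45 | 32 | 5 | 4 of 9 (44%) |
| 28 | 10 | 38 | 32.30 | 33 | 5 | 5 of 10 (50%) |
| 29 | 9 | 38 | 32.30 | 33 | 5 | 4 of 9 (44%) |
| 29 | 10 | 39 | 33.15 | 34 | 5 | 5 of 10 (50%) |

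**Precision of a night SD.** For n independent normal readings the relative standard error is about 1/√(2(n − 1)). The exact form is √(1 − c4²)/c4, where c4 is the usual small-sample constant for the SD.

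| n | Approximate | Exact | 95% CI factor on the SD |
|---|---|---|---|
| 10 | 23.6% | 23.9% | 0.69–1.83 |
| 9 | 25.0% | 25.4% | 0.68–1.92 |
| 5 | 35.4% | 36.3% | 0.60–2.87 |
| 4 | 40.8% | 42.2% | 0.57–3.73 |

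**Dependence on how the count is repaired.** Suppose the count became a minimum of 36 on the present schedule. Then 36 − 28 = 8 or 36 − 29 = 7 night readings would be guaranteed, and the problem would largely go. If the count were dropped, or set no higher than the 85% level, the 4 or 5 in the first table would stand. A denser schedule with the present count gives mixed results. These are illustrations only:

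- 42 day and 10 night readings (52 in all), at least 49 needed: 49 − 42 = 7 of 10 night readings.
- 56 day and 20 night readings (76 in all), at least 65 needed by the 85% clause: 65 − 56 = 9 of 20 night readings.

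**The same percentage applied by period, present schedule.** Day: 0.85 × 28 = 23.8 and 0.85 × 29 = 24.65, so at least 24 of 28 or 25 of 29. Night: 0.85 × 9 = 7.65 and 0.85 × 10 = 8.5, so at least 8 of 9 or 9 of 10. One lost night reading is allowed.

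**The case against.** The strongest reply is that the two conditions are joint. A recording with 32 to 34 valid readings fails the count of more than 48, so under the rule as written a half-empty night is not accepted. That is correct. A reader might infer from the 85% clause alone that the plan admits such recordings, and the full sentence does not support this. But the same sentence also rejects every complete recording, so it cannot be run as it stands, and the 85% clause is the only part the schedule can satisfy.

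A second reply is that repairing the count may cure the matter. For some repairs it does, as the minimum of 36 shows. It would be wrong to say that the weakness remains whatever count is chosen.

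Third, a condensed article may leave period-specific rules to the full protocol or to the operating procedures mentioned in section 2.6. That is possible. However, the article does state a completeness rule, and the rule it states is pooled.

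Fourth, section 2.7 names neither night variability nor dipping in any analysis, so the effect on the sodium and organ-damage results is inferred. This stands and limits the severity.

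**Conclusion.** The point holds as a cheap improvement of low to moderate severity. Completeness is judged over the whole day while indices are taken by period, and the count of more than 48 is out of reach on a 37 to 39 reading schedule. Under the 85% clause, 5 readings may be lost. In the worst case 4 of 9 or 5 of 10 night readings remain, and the relative standard error of the night SD rises from about 24–25% to 35–42%.

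This rests on the stated schedule being kept, on a reconciled count that does not itself limit night losses, on all losses falling at night, and on independent normal readings for the standard errors. The document does not say how often such recordings occur.

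A reader might also infer that true dippers would be relabelled nondippers. The document gives no night profile, so this depends on an assumed one. Take hourly night values of 132, 124, 118, 114, 113, 113, 114, 117, 124 and 131 (mean 120) and a day mean of 135, a fall of 15/135 = 11.1%. Losing five consecutive middle readings gives a night mean of 123.6 to 125.8 and a fall of 6.8% to 8.4%. Losing the first or last five leaves the class unchanged. But 135 and 120 are upper reference limits in section 2.5.3, not patient means, and they start the patient only 1.1 points above the cutoff. With the same profile shifted to a 15% fall (night mean 114.75), the largest shift of 5.8 gives about 120.6 and a fall of 10.7%, still a dipper. Relabelling is therefore possible near the cutoff but is not shown to be general.

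**What to change.** Make one edit to section 2.5.3:

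1. Reconcile the count of more than 48 with the measurement schedule.
2. Apply the requirement of more than 85% valid readings within day and within night, each for that period's mean, SD and CV.
3. Require both periods to meet it before dipping status is assigned.
4. Keep the pooled 24-hour rule for the 24-hour indices. A recording that fails only at night keeps its day and 24-hour values, and only its night and dipping values are set to missing.
5. Report the results from all recordings as a sensitivity analysis.

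No new measurement is needed. The cost is that some patients lose night and dipping values, because on the present schedule only one lost night reading is allowed. The losses may be selective, for example in patients with disturbed sleep, which is why the sensitivity analysis is part of the change.

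### The ambulatory blood pressure validity rule asks for more than 48 valid readings, but the stated schedule gives only 37 to 39 in 24 hours

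*Protocol article*

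**What the plan says.** Section 2.5.3 (Ambulatory blood pressure monitoring) of the protocol article sets the schedule in two parts. By day, pressure is "measured every 30 minutes during the day (8:00–22:00"; by night, readings are taken "every night at 22:01 to 7:59 the following day, every hour".

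The next sentence sets two conditions for a valid recording, joined by *and*:

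- a relative one: "The daily effective blood pressure reading is greater than 85% of the set number";
- an absolute one: "and the effective value needs to be greater than 48 times".

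The section gives no recording length as such. Its indicators are for 24 hours, day and night: "Monitoring indicators: 24-hour mean SBP (24-h SBP), 24-hour mean DBP (24-h DBP", followed by the day-time and night-time means. It then defines the variability measures: "The blood pressure standard deviation (SD) and its coefficient of variation (CV) at each time period were used as indicators of BPV". The dipper classification and the 12% cutoff for CV-SBP are in the same section.

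**The concern.** A validity rule for ambulatory monitoring should allow for some failed readings, so its threshold has to lie below the number programmed. Here the absolute threshold lies above that number. The two conditions also disagree with each other: one tolerates a loss of just under 15% of readings, while the other asks for more readings than are taken.

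Blood pressure variability is one of the three linked quantities in the study aim (section 2.1). Section 2.7 uses it in the covariance analysis and the stepwise regression. Every variability measure for the planned 600 patients depends on which recordings count as valid. A rule that cannot be met leaves that question without a usable written answer, and anyone who accepts a recording departs from the protocol as written.

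**Working it through.** **Inputs, all from section 2.5.3**

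- Day: every 30 minutes, 8:00 to 22:00 (14 hours).
- Night: every hour, 22:01 to 7:59 (about 10 hours).
- Relative condition: valid readings above 85% of the programmed number, per day.
- Absolute condition: valid readings above 48, so at least 49.
- Recording length: 24 hours, inferred from the indicators listed.

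**Step 1: day readings.** 14 h × 2 per hour = 28, or 29 if both 8:00 and 22:00 are counted.

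**Step 2: night readings.** Hourly from 22:01 (last at 7:01) or from 22:30 (last at 7:30) gives 10. On the clock hour, 23:00 to 7:00, gives 9.

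**Step 3: totals and thresholds.** Let N be the programmed total. The relative condition needs the smallest whole number above 0.85 × N. The absolute condition needs 49, whatever N is.

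| Day + night | N | 0.85 × N | Needed by the 85% rule | Needed by the count | 49 / N | Shortfall, 49 − N |
|---|---|---|---|---|---|---|
| 28 + 9 | 37 | 31.45 | 32 | 49 | 132% | 12 |
| 29 + 9 or 28 + 10 | 38 | 32.30 | 33 | 49 | 129% | 11 |
| 29 + 10 | 39 | 33.15 | 34 | 49 | 126% | 10 |

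Under every end-point convention, a recording with no failed reading at all still falls 10 to 12 readings short of the count. The 85% rule alone can be met: it allows 5 failed readings in each case (37 − 32, 38 − 33, 39 − 34).

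**Step 4: can another reading of the schedule rescue the count?**

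- *A 48-hour recording* would give 2 × 37 = 74 to 2 × 39 = 78 readings, which exceeds 48. No section mentions a recording of that length, the indicators are 24-hour ones, and the 85% condition is stated per day.
- *Half-hourly readings for the full 24 hours* would give 24 × 2 = 48, or 49 with both end points. This is not the stated schedule. Even then, the count would be met only if both end points are counted and no reading fails.

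**The case against.** The strongest reply is that the error does little harm. The same sentence contains a workable 85% rule, and a team that finds the count impossible may simply use that rule for everyone. Variability would then be computed from a uniformly selected set of recordings. This may well happen, but the protocol does not say so, and the two conditions are joined so that both must hold.

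Four stronger readings are tempting, and the document does not support them.

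- *All 600 recordings are lost, or every variability value is invalid.* No section says that a failing recording is excluded, repeated or replaced. What follows from the text is that the criterion cannot be met.
- *Staff will waive the rule case by case and so bias SD and CV.* This is possible, but nothing in the text shows it. Ignoring the count for everyone would involve no such selection.
- *The count is plainly the wrong figure.* The document does not show whether the count, the intervals or the time windows are misstated. The clause on night readings is awkwardly worded, so the schedule could be the faulty part.
- *The 85% rule ought to hold separately for day and night.* The protocol sets a daily rule, and the contradiction does not call for a change. With 9 or 10 night readings, a separate rule would need at least 8 of 9 (0.85 × 9 = 7.65) or 9 of 10 (0.85 × 10 = 8.5), so at most one failed night reading. That is materially stricter.

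It is also fair to say that the 24-hour length is inferred. The inference is well supported, for the reasons given under the 48-hour variant.

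**Conclusion.** The contradiction is certain and needs correcting. For a 24-hour recording on the stated schedule, the absolute condition needs at least 49 valid readings out of 37 to 39 programmed, and it fails under every way of counting the end points. The result rests on two assumptions: that the intervals and windows are as printed, and that a recording lasts 24 hours.

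The consequence is limited to this: the protocol has no validity rule that can be followed as written for the recordings behind the SD, CV, dipper class and CV-SBP grouping. Loss of all the variability data, or bias in them, is not shown.

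**What to change.** Before any recording is judged, confirm the intervals actually programmed in the monitors. Then state one attainable pair of schedule and threshold in section 2.5.3, and carry it into the standard operating procedure.

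- **If the schedule stands as written:** remove the count condition and apply the existing daily 85% rule uniformly. Give it as a number once the end-point convention is fixed: at least 32 of 37, 33 of 38 or 34 of 39.
- **If a count above 48 is intended:** correct the stated intervals so that the programmed total exceeds 48 with room for failed readings. For orientation, 48 / 0.85 = 56.5; with 57 programmed readings both conditions would ask for 49 (0.85 × 57 = 48.45).

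The choice belongs to the sponsor, because the document does not show which figure is wrong. No separate day and night rule is needed.

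If only the threshold is wrong, the cost is one sentence in the protocol and the matching line in the operating procedure, with no extra patients or procedures. If the printed intervals are wrong but the monitors are already set as intended, the cost is the same. Reprogramming would be needed only if the devices themselves follow a schedule that was not intended.

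### The raw 24-hour SD and CV count the normal night-time fall as blood pressure variability, and neither the 12% CV grouping nor the analyses name a period that would exclude them

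*Protocol article*

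**What the plan says.** All of the relevant definitions stand in section 2.5.3 of the protocol article (Ambulatory blood pressure monitoring).

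- **Periods monitored:** "24-hour mean SBP (24-h SBP), 24-hour mean DBP (24-h DBP), day-time mean SBP, night-time mean SBP, day-time average DBP, and night-time mean DBP".
- **BPV index:** "The blood pressure standard deviation (SD) and its coefficient of variation (CV) at each time period were used as indicators of BPV", each for its own period. The 24-hour SD and CV are thus one of three sets of BPV indices, beside the day and night sets.
- **CV formula:** "Expressed by the formula: CV = σ/μ". No weighting by day and night is attached.
- **Grouping:** "CV-SBP is grouped with a cutoff of 12" per cent. The abbreviation is expanded only as "CV-SBP, coefficient of variation of systolic blood pressure", without a period.
- **Dipping:** a relative day-to-night fall of ">10% is normal blood pressure circadian rhythm (dipper type hypertension"). It is classified separately from BPV.
- **Schedule:** "measured every 30 minutes during the day (8:00–22:00), every night at 22:01 to 7:59 the following day, every hour".

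Section 2.7 (Statistical methods) compares BPV between groups by covariance analysis and runs stepwise regression on target organ factors related to BPV. It does not say which period's BPV enters either analysis.

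**The concern.** The total variance of readings over 24 hours has two parts: variation within day and within night, and a part that grows with the square of the day-night difference. A patient whose pressure falls normally at night therefore has a larger 24-hour SD and CV than a non-dipper with the same SDs within day and night.

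The protocol regards dipping as the normal pattern, and its Discussion links higher BPV to worse TOD. An index that rises with dipping mixes a feature regarded as favourable into a measure regarded as unfavourable. If that index forms the 12% groups or enters the section 2.7 analyses, high BPV will partly mean a deep nocturnal fall, and the relation with TOD, which is central to the study's aim, is blurred.

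The schedule raises a related matter. Readings are twice as frequent by day as by night, so a plain average of all readings gives the day more than its share of the 24 hours.

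**Working it through.** The protocol gives no figure for this point, so there is none to reproduce. The check is a variance decomposition.

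**Inputs from section 2.5.3.** Day 08:00–22:00 (14 h), half-hourly; night 10 h, hourly; cut-off 12%; normal fall above 10%. Counting intervals gives 28 day and 10 night readings. Counting both end points of the day gives 29, with 9 or 10 at night.

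**Assumed inputs (not in the protocol).** Day mean SBP 140, day SD 14, night SD 12 mmHg, all held fixed while the fall d varies.

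**1. Raw 24-hour CV, 28 day and 10 night readings.** The night mean is 140(1−d), and m is the mean of all 38 readings.

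Variance = [27×14² + 9×12² + 28(140−m)² + 10(night mean−m)²] / 37

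The within-period sum of squares is 5292 + 1296 = 6588 in every row.

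| Fall | m (mmHg) | Between-period sum of squares | 24-h SD (mmHg) | 24-h CV |
|---|---|---|---|---|
| 0% | 140.0 | 0 | 13.3 | 9.5% |
| 10% | 136.3 | 1444 | 14.7 | 10.8% |
| 15% | 134.5 | 3249 | 16.3 | 12.1% |
| 20% | 132.6 | 5777 | 18.3 | 13.8% |

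Example at 15%: √[(6588 + 3249)/37] = 16.3, and 16.3/134.5 = 12.1%.

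**2. Sensitivity to the reading count.** At a 15% fall the CV is 12.1% with 29 day and 10 night readings and 11.97% with 29 and 9. The 12% line is crossed at a fall of about 14.6%, 14.7% and 15.1% for the three counts.

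**3. Sensitivity to the within-period assumption.** Let w be the within-period CV, equal by day and night, and p = 29/39 the day share of readings. Then

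24-h CV = √[p·w² + (1−p)·w²(1−d)² + p(1−p)·d²] / [1 − (1−p)d]

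With w = 10% this gives 10.0%, 11.0%, 12.1% and 13.6% at falls of 0, 10, 15 and 20%. At the last three, the fall supplies 17%, 32% and 46% of the 24-hour variance. The w needed to reach 12% is 12.0%, 11.1%, 9.9% and 7.7%. The fall alone (w = 0) gives 4.5%, 6.8% and 9.2% at 10, 15 and 20%, so it does not reach 12% without other variability.

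**4. Duration-weighted alternative, inputs of step 1.** SD = (14×14 + 10×12)/24 = 316/24 = 13.2 mmHg at every fall. Its CV on the time-weighted mean is 13.17/140 = 9.4% with no fall, 13.17/131.25 = 10.0% at 15% and 13.17/128.33 = 10.3% at 20%. It still rises a little, because the mean falls, but far less than the raw CV.

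**5. Effect on grouping and association (illustrative simulation).** Assumed: N = 600, w distributed as 10% ± 2%, fall as 8% ± 7%, independent of each other. Above 12% on the raw 24-hour CV are 54% of dippers and 20% of non-dippers, against 16% of each on the within-period CV. Replacing the within-period CV by the raw 24-hour CV lowers the correlation with TOD from 0.29 to 0.24 if the fall is unrelated to TOD. It lowers it from 0.27 to 0.09 if a larger fall goes with less TOD (0.3 SD less per SD of fall).

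**6. 24-hour mean.** The excess of an unweighted mean of readings over a time-weighted mean is (28/38 − 14/24) × fall = 0.1535 × fall, or 3.1 mmHg for a 20 mmHg fall. With 29/39 it is 3.2 mmHg, and with 29/38 it is 3.6 mmHg.

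**The case against.** The strongest reply is that the protocol does not make the 24-hour SD and CV its only measure of BPV. Day and night indices are specified alongside them and are free of the day-night term. This stands: the problem concerns one of three sets.

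Second, no passage ties the 12% grouping or the section 2.7 analyses to the 24-hour index. A reader might infer that dippers will be misclassified; the text does not support that as a fact. If the day or night CV is meant, the problem does not arise. A condensed article may also leave the choice of analysis variable to a fuller document. Silence on the period would therefore not be a finding alone. The finding is that the article itself fixes a 24-hour index with an unweighted formula, and that index scores a normal fall as variability.

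Third, a reader might infer that the BPV–TOD association is biased to zero or beyond. Nothing here shows that. Neither simulated case passes zero, and both rest on distributions that the protocol does not give. Nor does the protocol give any salt–dipping relation from which to claim distortion of the salt–BPV link.

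Fourth, the weighted CV also rises slightly with the fall (9.4% to 10.3%), and the protocol offers no basis for 12% on that index. Both are correct, and they are reasons to place the cut-off on a named within-period CV.

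Fifth, section 2.5.3 does not say that the 24-hour mean is a plain average. The schedule behind the 3 mmHg figure also conflicts with the same section's requirement of more than 48 valid readings, since at most 38 or 39 are scheduled. The figure is conditional on both points.

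**Conclusion.** The point holds in a conditional form. The raw 24-hour SD and CV, as defined, include the day-night difference, and nothing in the protocol removes it. If they are used for the 12% grouping or in section 2.7, patients with a normal circadian pattern can be classed as high BPV. This needs a within-period CV of about 11% at a 10% fall, 10% at 15% or 8% at 20%. In the worked example the crossing comes at a fall of about 15%. Attenuation of the BPV–TOD association is the probable consequence; its size depends on how the fall relates to TOD, which the document does not give.

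All participants are hypertensive, so \"normal\" here describes the circadian pattern only. The matter is a cheap improvement worth making, not a flaw that undermines the design.

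**What to change.** 1. In section 2.5.3, define 24-hour BPV as the duration-weighted SD, (14 × day SD + 10 × night SD)/24. Keep the raw 24-hour SD as a secondary display.
2. Name the period for CV-SBP at the 12% cut-off and for BPV in the covariance and regression analyses. Use a within-period index, for example the daytime CV, and not the raw 24-hour CV. State the basis for 12% on the index chosen.
3. Compute the 24-hour mean with time weights before comparing it with the 24-hour reference value.
4. Reconcile the reading schedule with the requirement of more than 48 valid readings, since the two cannot both hold as written.

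The cost is a few sentences of protocol text and a few lines of derivation code; the readings already planned suffice. The downside is less direct comparability with papers that report the raw 24-hour SD, which the secondary display largely covers.

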**Objective::**

The purpose of this study is to compare 24-hour urine sodium excretion, BPV, carotid intima–media thickness, left ventricular mass index, and serum creatinine or endogenous creatinine clearance rate. To clarify the relationship between high salt load and BPV and TOD in patients with hypertension.

This study is a cross-sectional study. It will recruit 600 patients with essential hypertension in the outpatient and inpatient department of cardiovascular medicine of Chengdu Fifth People's Hospital. Researchers will obtain blood and urine samples with the patient's informed consent. In addition, we will measure patient's blood pressure and target organ-related information.

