### Statistical methods

2.7

We will use SPSS 17.0 software for statistical analysis in this study. Normal distribution measurement data was expressed as mean ± SD. One-way analysis of variance was used for comparison of means among multiple groups, and SNK test was used for pairwise comparison. The measurement data of non-normal distribution is expressed as median M (P25–P75). After the natural logarithm is converted to the normal distribution data for analysis, the nonparametric statistical method is used for comparison between groups. Nonparametric test was used to compare data between groups. Correlation analysis used Pearson correlation analysis. Covariance analysis was used to compare the differences in BPV between groups, and multiple stepwise regression analysis was performed on target organ factors related to BPV. *P* < .05 is statistically significant.

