## Discussion

3

Hypertension is a major cause of many chronic and life-threatening diseases, such as cardiovascular disease and kidney failure. However, due to mild nonspecific symptoms, awareness is relatively low and patient compliance and control is poor. Hypertension is a complex syndrome affected by many genetic and environmental factors. Many epidemiological studies have shown a significant relationship between salt intake and blood pressure.^[12,13]^

BPV is associated with an increased risk of clinical TOD, such as cardiovascular and renal damage, and an increase in cardiovascular mortality.^[14]^

Blood pressure exhibits highly observed oscillations.^[15]^ There are 3 different types of BPV, depending on the time period in which it occurs: very short-term BPV, short-term BPV, and long-term BPV.^[16]^ Average consolidation rate (ARV) was introduced as a new BPV index. The ARV is the sum of the differences between every 2 consecutive readings. A systematic review of ARV assessment studies at 24 hour BPV was conducted in 19 studies, of which 17 reported a significant correlation between high ARV and TOD.^[17]^ In all these studies, BPV remained a significant independent predictor of all cardiovascular events.^[17]^ The increase of BPV in hypertensive patients is significantly correlated with the increase of TOD severity. Subsequent studies have shown that an increase in BPV is associated with an increased risk of cardiovascular events.^[18,19]^ It is speculated that TOD is not only associated with uncontrolled hypertension, but also with increased BPV. Whether the mechanism of TOD mediated by hypertension is caused by changes in blood pressure remains unclear. Our present protocol will provide a new sight in the association between among high salt intake, BPV, and target organ damage in patients with essential hypertension.

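### Nothing in the plan ensures that mean blood pressure enters the analysis of blood pressure variability (BPV) and organ damage, so BP level can pass for an effect of variability

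*Protocol article*

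**What the plan says.** Section 2.5.3 defines the exposure: "The blood pressure standard deviation (SD) and its coefficient of variation (CV) at each time period were used as indicators of BPV". It adds that "CV is the ratio of the SD to the mean". The same section records mean systolic and diastolic pressure over 24 hours, by day and by night, as monitoring indicators.

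Section 2.7 names three relevant methods:
- "Correlation analysis used Pearson correlation analysis", without saying which variables are paired.
- "multiple stepwise regression analysis was performed on target organ factors related to BPV", without listing candidate variables or any variable kept in the model.
- Covariance analysis, for differences in BPV between groups only, with no covariate named.

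The rationale separates variability from level. The Introduction holds that BPV is tied more closely to organ damage than BP level is. The Discussion says: "It is speculated that TOD is not only associated with uncontrolled hypertension, but also with increased BPV".

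**The concern.** Mean BP plausibly contributes to left ventricular mass, carotid thickness and albuminuria. If SD also rises with the mean, SD will correlate with organ damage even when variability has no effect of its own. A Pearson correlation cannot tell the two apart. Dividing by the mean, as CV does, removes level only when SD is proportional to the mean. Otherwise CV gains its own link with level, possibly opposite in sign to that of SD.

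At stake is the interpretation. The study could report that BPV goes with organ damage when only BP level does, and its two BPV indices could disagree for an artefactual reason.

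**Working it through.** **Inputs from the documents.** "It will recruit 600 patients with essential hypertension" (abstract, Objective); significance at 0.05 (section 2.7), taken as two-sided because sidedness is not stated. No effect size, power or correlation accompanies the 600, so there is no planned figure to reproduce.

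**Assumed inputs.** Let *a* = corr(mean BP, SD) and *b* = corr(mean BP, organ damage). Neither is in the documents. The ranges used are *a* = 0 to 0.5 and *b* = 0.2 to 0.4.

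**Step 1: threshold.** By Fisher's z, a correlation is significant at n = 600 when |r| ≥ tanh(1.96/√597) = 0.080.

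**Step 2: correlation induced through BP level.** If SD has no effect of its own, r(SD, organ damage) = a × b. The chance of significance is about Φ(√597·atanh(ab) − 1.96), plus a small opposite tail. Example: a = b = 0.3 gives ab = 0.09; 24.43 × 0.0902 = 2.20; Φ(0.24) ≈ 0.60. In full:

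| *a* | *b* = 0.2 | *b* = 0.3 | *b* = 0.4 |
|---|---|---|---|
| 0.1 | 7.8% | 11.3% | 16.5% |
| 0.2 | 16.5% | 31.2% | 50.0% |
| 0.3 | 31.2% | 59.7% | 83.8% |
| 0.4 | 50.0% | 83.8% | 97.6% |
| 0.5 | 68.8% | 95.8% | 99.9% |

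**Step 3: CV and adjustment, by simulation.** 2,000 runs per row; n = 600; *b* = 0.3; assumed mean SBP 135 (SD 14) and within-person SD 14 (SD 3.5); organ damage depends on mean BP only. Entries are the percentage of runs in which the BPV index is falsely significant. In the last column, mean BP and SD are the only candidates (assumed entry 0.05, removal 0.10).

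| *a* | Pearson, SD | Pearson, CV | corr(CV, mean) | SD, mean forced in | CV, mean forced in | SD, stepwise with mean offered |
|---|---|---|---|---|---|---|
| 0 | 5.2 | 80.2 | −0.39 | 5.4 | 5.2 | 5.4 |
| 0.2 | 33.0 | 35.8 | −0.22 | 4.8 | 4.6 | 4.8 |
| 0.3 | 59.6 | 15.1 | −0.12 | 5.0 | 4.8 | 5.0 |
| 0.4 | 84.7 | 5.4 | −0.02 | 5.2 | 5.3 | 5.2 |
| 0.5 | 95.7 | 11.2 | +0.10 | 5.2 | 5.2 | 5.2 |

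The near-nominal CV result at *a* = 0.4 is expected. The slope of SD on the mean is a × 3.5/14 = 0.25a, and proportionality needs a slope of 14/135 = 0.104, which is reached at a = 0.104/0.25 = 0.41. On either side of that value CV carries level, with opposite signs.

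**Step 4: a different model.** Here SD varies as mean^p with p = 0.5, 1 or 1.5, a between-person spread of 22% and 28 readings, all assumed. With *b* = 0.3 to 0.4, false significance was 29% to 99.7% for SD and 5% to 48% for CV. With *b* = 0.1 to 0.3 it was 7% to 96% and 4% to 30%. With log SD and log mean in one model it was 4% to 6% throughout.

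**Step 5: does stepwise selection lose mean BP?** Hardly, if it is offered. At *b* = 0.3, t = 0.3 × √598/√(1 − 0.09) = 7.7. In the step 4 model with *b* = 0.3 to 0.4, mean SBP was kept in every run and SD was falsely selected in 4.9% to 5.7%. With *b* = 0.1 to 0.3 the error was about 5% to 8%; mean BP was left out appreciably often (30% to 36% of runs) only at *b* = 0.1.

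**The case against.** The strongest reply is that section 2.7 does not make Pearson correlation the BPV and organ-damage analysis. It names no pairs for the correlation, and the one sentence that joins BPV to target organs describes a multivariable regression. That stands. A reader might infer that BPV will be judged by correlation alone, or that the high rates in step 2 apply to the planned regression; the text supports neither.

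A reader might also infer that stepwise selection would discard mean BP. Step 5 shows that this risk is minor when mean BP is a candidate, though only two candidates were tried.

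Next, silence is not exclusion. This is a condensed article, and a fuller protocol or analysis plan may list covariates. That also stands: the documents do not show that mean BP is left out. The point survives because the article does fix its methods, and an unadjusted correlation or an open stepwise search is a weaker choice than a model in which the mean is fixed.

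Finally, the stated objectives (abstract and section 2.1) speak only of clarifying or investigating a relationship, and the Discussion sentence is background. So the documents do not define an estimand of BPV independent of BP level. They do motivate the study by that distinction, and results will be read in its light.

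**Conclusion.** The point holds as a moderate weakness; the documents do not support calling it a must-fix defect. Nothing stated in the plan ensures that mean BP is in the BPV and organ-damage analysis, although the means are recorded and the rationale sets variability apart from level. If an unadjusted correlation of SD with organ damage is reported, BP level alone could make it significant in roughly 10% to over 90% of studies at n = 600. That range rests wholly on the assumed *a* and *b*, and the inflation vanishes for SD when *a* = 0. CV protects only near proportionality of SD and mean. The direction of the problem is robust; its size is not known from the documents.

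**What to change.** In section 2.7, state that each regression of an organ-damage measure on SD or CV includes, as a forced term, the mean BP of the same period already recorded under section 2.5.3. State that conclusions about BPV rest on that adjusted coefficient, and that Pearson correlations of SD and CV with organ damage are descriptive. Using logs of SD and mean is optional.

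This takes about two sentences and no new data. The price is a somewhat wider interval for BPV. For SD, the ratio of adjusted to unadjusted standard error is √[(1 − b²)/((1 − a²)(1 − a²b²))]. With *b* = 0.3 this is 1.00 at *a* = 0.3 and 1.11 at *a* = 0.5. A single day's mean is an imperfect measure of usual BP, so adjustment reduces the carry-over from level and may not remove all of it.
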